## Abstract

**Background:**

Two different approaches have been adopted when applying motor imagery (MI) to stroke patients. MI can be conducted either added to conventional physiotherapy or integrated within therapy sessions. The proposed study aims to compare the efficacy of embedded MI to an added MI intervention. Evidence from pilot studies reported in the literature suggests that both approaches can improve performance of a complex motor skill involving whole body movements, however, it remains to be demonstrated, which is the more effective one.

**Methods/Design:**

A single blinded, randomised controlled trial (RCT) with a pre-post intervention design will be carried out. The study design includes two experimental groups and a control group (CG). Both experimental groups (EG1, EG2) will receive physical practice of a clinical relevant motor task ('Going down, laying on the floor, and getting up again') over a two week intervention period: EG1 with embedded MI training, EG2 with MI training added after physiotherapy. The CG will receive standard physiotherapy intervention and an additional control intervention not related to MI.

The primary study outcome is the time difference to perform the task from pre to post-intervention. Secondary outcomes include level of help needed, stages of motor task completion, degree of motor impairment, balance ability, fear of falling measure, motivation score, and motor imagery ability score. Four data collection points are proposed: twice during baseline phase, once following the intervention period, and once after a two week follow up. A nested qualitative part should add an important insight into patients' experience and attitudes towards MI. Semi-structured interviews of six to ten patients, who participate in the RCT, will be conducted to investigate patients' previous experience with MI and their expectations towards the MI intervention in the study. Patients will be interviewed prior and after the intervention period.

**Discussion:**

Results will determine whether embedded MI is superior to added MI. Findings of the semi-structured interviews will help to integrate patient's expectations of MI interventions in the design of research studies to improve practical applicability using MI as an adjunct therapy technique.

**Trial registration:**

ClinicalTrials.gov NCT00858910

## Background

Regardless of the decreasing trend in long-term statistics stroke is still one of the three leading causes of death in the US [1] and in Europe. The incidence for individuals older than 55 years range from 4.2 to 11.7 per 1000 [2]. Stroke has a sudden onset resulting from cerebral haemorrhage or ischemia in the brain. In the US, 600'000 first-ever strokes occurred in 2005 with an estimated cost to the community of $ 65 billion in both direct and indirect costs in 2008 [1,3]. In Europe the total costs of stroke are aggregate to 38 € billions in 2006: 49% arise from direct costs, 23% from productivity loss, and 29% from the formal care [4]. Only 25% of the affected individuals recover with minor problems, 45% sustain moderate to severe impairments that necessitate special attention and lifelong care [5].

Several rehabilitation methods address patient recovery, are based on motor learning or neuro-developmental approaches [6-11]. Physiotherapy focuses on regaining motor function, postural alignment and independence in activities of daily living (ADL). Regaining functional ability with a focus on mobility is one of the most frequently targeted short-term rehabilitation goals in patients [12]. New rehabilitation approaches have been reported, e.g. robot-aided [13], virtual reality rehabilitation [14], and MI [15,15]. MI does not require expensive technology, equipment, instrumented locations, and it does not physically exhaust the individual [16]. After initial learning, the MI technique can be practiced by the patient independent from the therapist, location, and time of the day.

The literature on MI techniques has increased tremendously since the late 1990s and there have been several literature reviews related to the application of stroke [17-19]. All found a beneficial value for the recovery of stroke patients when MI was added after physiotherapy or occupational therapy sessions. The analysed randomised or clinical controlled trials used different MI methodologies and compared MI versus an equivalent amount of attention time, where patients listened to information about stroke and relaxation exercises.

MI has its origin in the sports psychology and behavioural psychology in the end of the 19th century [20]. It involves rehearsing a known motor act without any visible muscle contraction or motor output [21]. Several theories are proposed to explain the neuro-physiological mechanisms of MI. The 'psycho neuromuscular theory' was proposed by Jacobson in the early 1930s based on the detection of myoelectrical changes related to the imagined movement [22]. Another theory is based on co-location of brain activation during imagined and real movements in healthy individuals [23-25] as well as in stroke patients [26,27]. Functional magnetic resonance imaging (fMRI) showed activation in frontal, parietal cortical, and sub-cortical areas that are involved in action planning, execution and modulation [25,28]. Recently, the first fMRI study was published that investigated brain activation during imagination of whole body movements [29], supporting the findings from many MI intervention studies in sport psychology.

To date intervention studies in stroke rehabilitation have focused on simple movements, such as reaching and grasping [15,30], whereas investigations in sports psychology used more complex motor skills [31]. Complex motor activities are relevant in rehabilitation as well, since patients seek to regain independence in ADL. Previous stroke research has compared MI to a different mental practice method, e.g. relaxation, or listening to information about stroke. Some researchers have added MI to conventional physiotherapy or occupational sessions [17]. More recently, study proposals were published that will investigate the effect of embedded MI in more complex tasks of daily living [32,33]. Holmes and Collins developed the PETTLEP model to embed MI in training for sports psychology in 2001 [34] based on a combination of seven real-life conditions: physical, environment, task, timing, learning, emotion, and perspective. The PETTLEP model has improved outcome when applied in a MI intervention [35,36]. MI training may be embedded into physiotherapy sessions offering the prospect of more effective and systematic MI training compared to added MI approaches. However, to the authors' knowledge, the PETTLEP model has not been adapted and tested in a stroke population.

Aside the quantitative assessment of MI it is essential to determine patients' experiences with this training method. In sports research the athlete's usage of imagery was assessed with semi-structured interviews, e.g. during rehabilitation of an injury [37] as well as during and after training periods [38]. Driediger et al. [37] reported positive effects of imagery regarding cognitive, motivational, and healing intentions in those athletes. Imagery was used frequently during the day, during rest, e.g. before sleeping, and various other activities such as car driving. Positive and exact images were used to set goals for the rehabilitation process, to handle pain intensity, and to keep a positive stance. These studies found that interviewed athletes were experienced and knowledgeable about imagery and made frequent use of different imagery types, e.g. kinaesthetic, visual, and auditory imagery. Research is needed to transfer these qualitative findings from sports to a stroke population.

### Study aims and research questions

This study consists of a quantitative part and a qualitative part. The quantitative part is formed by a therapy intervention with a randomised controlled trial (RCT) study design. The RCT includes three study groups to evaluate the effect MI training embedded into physiotherapy versus MI training added to physiotherapy. In the qualitative part semi-structured interviews of six to ten patients who participate in the RCT will be interviewed to gain knowledge about the patient's experiences and expectations regarding MI. These study parts are compatible to each other and the results are expected to interact. Consequently, the overall study design has been described as a 'mixed methods approach'. Figure 1 illustrates the planned project.

**Figure 1 F1:**
[figure not shown]
**Study overview**. MI = motor imagery, BL, T0 = 1^st ^and 2^nd ^baseline measurement event, EG1, EG2 = experimental group 1 and 2, CG = control group, T1 = measurement event after the 2 week intervention period, FU = measurement event after a 2 week follow-up period.

The following sections describe the research protocol of both parts in detail.

#### Aim of the quantitative study part

The aim of the study part is to compare the effect of embedded MI training in physiotherapy (EG1, PETTLEP approach) to added MI (EG2) after regular physiotherapy sessions, regarding improvements of time needed to perform a motor task ('Going down, laying on the floor, and getting up again'). A third patient group with no MI will serve as a control group (CG) to provide an overall baseline for this intervention.

(EG1= experimental group 1, EG2 = experimental group 2)

#### Research question of the quantitative study part

Do patients in the embedded MI training group (EG1) require less time to perform the motor task compared to patients in the added MI training group (EG2)?

#### Aim of the qualitative study part

This qualitative part of the study should add an important insight into patients' experience and attitude to imagery, especially MI. With the help of semi-structured interviews the following aspects will be investigated:

- Before MI intervention:

∘ Patient's previous experience with MI.

∘ Patient's usage of MI regarding the 'W-questions' in imagery research (When, Where, What, Why) [39].

∘ Patient's expectations towards the MI intervention in the RCT.

- After MI intervention:

∘ Patient's attitudes towards the MI after the intervention.

∘ Patient's tentative changes in MI usage.

#### Research question of the qualitative study part

What are the thoughts, feelings, and experience of people with stroke who are participating in MI training? Does it change after a two week MI intervention?

## Methods

### Methodology of the quantitative study part

#### Quantitative study design and setting

In this single-centred randomised controlled trial with a pre-post intervention design, embedded and added MI techniques will be compared to improve a learned motor task ('Going down, laying on the floor, and getting up again'; for a detailed description please see Section 'Motor task and fear of falling on page 13). The study design includes two experimental groups and one control group. Both experimental groups (EG1, EG2) will receive physiotherapy for the motor task: EG1 with an embedded MI training into physiotherapy sessions (PETTLEP approach), EG2 with an added MI training after physiotherapy. The third group is the control group (CG) with physiotherapy and an added control intervention not related to MI. All groups receive the same intervention time of 45 minutes. The investigation will have an intervention period of two weeks and will be carried out in the rehabilitation centre Reha Rheinfelden in Switzerland.

The study has been approved by the responsible cantonal review board of the health department Aarau (Switzerland) and the ethics committee of the School of Health and Social Care at Oxford Brookes University (United Kingdom).

#### Primary and secondary outcome measures

Table 1 provides an overview on all study outcome measures. All outcome measures will be assessed at four times: twice during the baseline phase (BL, T0), after the intervention (T1), and after the two week follow-up phase (FU). Changes over time will be calculated by the differences between BL vs. T0, T0 vs. T1 and T1 vs. FU.

**Table 1 T1:** Overview study endpoints and outcome measures

	**Primary outcome**	**Primary outcome measure:**
	Time difference between T0 and T1 needed to perform the motor task ('Going down, laying on the floor, and getting up again')	Time will be given in seconds and will be obtained by the recorded video of the task performance.

	**Secondary outcome**	**Secondary outcome measures**

**1**	Time difference between BL vs. T0 and between T1 vs. FU	Time will be given in seconds and will be obtained by the recorded video of the task performance.

**2**	Help needed to perform the motor task	Assistance levels of the activity scale of the Chedoke McMaster Stroke Assessment (CMSA)

**3**	Stage of the motor task	Stage of the motor task by Bergland and Lake will be obtained by the recorded video of the task performance.

**4**	Imagination inflation	Patients will be asked before each motor task execution during the assessments to predict time they expect to need to perform the motor task.

**5**	Motor impairment and independence	German version of the extended Barthel index (EBI)

**6**	Balance	German version of the Berg Balance Scale (BBS)

**7**	Motor imagery ability	German version of the kinesthetic and visual motor imagery questionnaire (KVIQ-G)

**8**	Understanding of the motor imagery instructions	German version of the Imaprax software version 1.1

**9**	Fear of falling (FOF)	German version of the Activities-Specific Balance Confidence Scale (ABC-scale)

**10**	Intrinsic motivation	Motor imagery diary

**11**	Mood	Direct question that can be answered on an 11-point VAS: 'How sad do you feel today?'

All outcome measures will be assessed at four times to measure changes over time: twice during the baseline phase, after the intervention, and after the two week follow-up phase.

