##### Primary outcome measure

The primary study outcome has been defined as changes in time needed to perform the motor task due to the study intervention. This primary outcome will be assessed by the difference between measurement points T0 and T1. For performance and validity reasons all assessment sessions will be videotaped. Time needed to perform the task in seconds will be derived from the video recordings.

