##### Motor task related profile

1. Time difference to perform the motor task between BL and T0 as well as between T1 and FU.

2. Help needed to perform the motor task will be evaluated using classification levels of the activity scale of the Chedoke McMaster Stroke Assessment (CMSA) [40,41]. The CMSA is a validated and very reliable performance-based assessment [42-44]. The activity scale belongs to the gross function index and is scored with one (patient needs total assistance or the task is not tested for safety reasons) to seven (patient can perform the task completely independent without any assistance or devices, in a reasonable time) on an ordinal scale [45].

3. Stage of the motor task will be evaluated using the classification of Bergland and Laake [46] (please see section 'Stages of the motor task').

4. 'Imagination inflation': Undergraduate college students overestimated their motor performance after MI training. This effect is called 'Imagination inflation' and was detected by Landau et al [47]. To monitor the inflation in this investigation all patients will be asked before each motor task execution during the assessments to predict time they will need to perform the task before each motor task execution.

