#### Study procedure and measurement events

The study procedure and all measurement events are illustrated in Figure 1. After signing informed consent, patients will start with the baseline phase that extends over week 1 and week 2. During this time patients will undergo all clinical measurements twice (BL, T0) at an interval of six to seven days. After the baseline phase all patients will be randomised to one of three study groups: EG1, EG2, or CG. Each group will receive three therapy sessions per week for two weeks, hence six sessions in total. Each session lasts 45 minutes. Based on the main study hypothesis, therapy for EG1 will embed MI training during physiotherapy, while EG2 will receive MI training after the physiotherapy part. For a detailed description please see Section 'Study intervention' on page 14. Baseline measurements will be repeated directly after the therapy session weeks to evaluate short-term effects of the MI intervention (T1), as well as after a follow up period of two weeks (FU). All intervention and assessment sessions will take place at the rehabilitation centre's physiotherapy department.

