#### Statistical analyses

All necessary statistical analyses will be performed with the Statistical Package for the Social Sciences (SPSS) version 16. The significance level will be set at p ≤ 0.05. For all outcome measures the final analysis method will be determined after data collection tests of normal distribution and homogeneity of variances. Before data analyses collected patient data will be anonymised.

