##### Group comparison

Group equality will be determined at baseline regarding all descriptive variables: age, gender, disease, affected brain hemisphere, time since stroke onset, cognitive function, handedness, rehabilitation history, patient's sports history, and patient's history of falls since stroke onset (over the last six to twelve months). Parametric and nonparametric tests will be used depending on statistical data level and data distribution. Furthermore, inter-group comparisons between BL and T0, T0 and T1, as well as T1 and FU will be calculated to analyse changes among all three groups over time. Additionally, intra-group comparisons for each measurement event (pre- and post-intervention; T0 vs. T1 vs. FU) will be calculated for all three groups; means, standard deviations and confidence intervals, will be given where feasible. An intention to treat analysis will be performed for drop outs. Missing values will be replaced by the average trend of all participants of the respective group.

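### At follow-up the arms are compared only on change since T1; the effect retained from T0 to FU has no planned between-group estimate

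*Protocol article*

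**What the plan says.** Under Primary and secondary outcome measures, change is defined for all outcomes over adjacent visits only: "Changes over time will be calculated by the differences between BL vs. T0, T0 vs. T1 and T1 vs. FU". The primary outcome uses the middle interval: "This primary outcome will be assessed by the difference between measurement points T0 and T1". Secondary outcome 1 takes the other two. Table 1 lists it as "Time difference between BL vs. T0 and between T1 vs. FU", and the motor task related profile repeats it: "Time difference to perform the motor task between BL and T0 as well as between T1 and FU".

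The Group comparison section carries the same intervals into the analysis: "inter-group comparisons between BL and T0, T0 and T1, as well as T1 and FU will be calculated". T0 and FU meet only inside each arm: "intra-group comparisons for each measurement event (pre- and post-intervention; T0 vs. T1 vs. FU) will be calculated for all three groups". FU falls two weeks after the intervention period. Allocation takes place after T0 (Study procedure and measurement events; Randomisation and allocation concealment), so BL-T0 lies wholly before randomisation.

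No section plans a between-group comparison of T0 with FU, or of FU adjusted for T0.

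**The concern.** T1 is measured after treatment. A change that starts there measures how much is lost or added from a level the arms may have reached differently. An arm with a larger gain has more to lose, so a smaller loss in the other arm can look like an advantage although its patients are worse off at FU. Both T0-T1 and T1-FU also contain the T1 measurement, so a chance good result at T1 tends to reappear as loss by FU.

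At stake is the follow-up answer to the trial's own question, embedded against added imagery. Patients return at FU, yet which arm is better off then, relative to the pre-treatment level, has no planned between-group comparison.

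Two smaller points come from the same sentences. A group difference in BL-T0 change can only be chance. And within-group comparisons in three arms do not estimate a difference between arms.

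**Working it through.** **Inputs.** From the article: the three intervals, the timing of randomisation, and the significance threshold ("The significance level will be set at p ≤ 0.05"). It gives no sample size, SD, effect size or power, so there is no figure of its own to reproduce. All seconds, retention fractions, SDs, correlations and arm sizes below are assumptions for illustration.

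**1. Expected contrasts.** Let g1 and g2 be the true gains (seconds saved, T0 to T1) in EG1 and EG2, and r1 and r2 the fractions retained at FU. Positive values favour EG1.

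- T0-T1 difference: g1 − g2
- T1-FU difference: (r1 − 1)g1 − (r2 − 1)g2
- T0-FU difference: r1·g1 − r2·g2, the sum of the two above

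With equal retention r, T1-FU is (r − 1)(g1 − g2), which goes against the arm that gained more for any r below 1. T0-FU is r(g1 − g2), which keeps the right sign for any r above 0.

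With g1 = 10 s and g2 = 5 s:

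| EG1 retained | EG2 retained | T1-FU | T0-FU |
|---|---|---|---|
| 25% | 25% | −3.75 s | +1.25 s |
| 50% | 50% | −2.5 s | +2.5 s |
| 70% | 70% | −1.5 s | +3.5 s |
| 90% | 90% | −0.5 s | +4.5 s |
| 100% | 100% | 0 s | +5 s |
| 70% | 100% | −3.0 s | +2.0 s |
| 80% | 60% | 0 s | +5.0 s |
| 90% | 50% | +1.5 s | +6.5 s |

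The T1-FU contrast goes against EG1 when its absolute loss is larger, that is when (1 − r1)g1 > (1 − r2)g2. It need not do so, as the last row shows.

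**2. Sampling behaviour.** Assume SD 10 s at each visit, common visit correlation ρ, n per arm, and 70% retention in both arms. The standard error of a group difference in change is 10·√(2(1 − ρ))·√(2/n).

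- ρ = 0.5, n = 10: 4.47 s. Chance that T1-FU favours the arm that gained less: Φ(1.5/4.47) = 63%. Chance that T0-FU favours the better arm: Φ(3.5/4.47) = 78%.
- ρ = 0.9, n = 20: 1.41 s. The same chances are Φ(1.5/1.41) = 86% and Φ(3.5/1.41) = 99%.

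A simulation of 20,000 trials per setting (ρ 0.5, 0.7, 0.9; n 10, 13, 20) gave the same ranges, 63% to 86% and 78% to 99%. Power for the 3.5 s T0-FU difference was only 12% to 70%, so the better contrast would still be imprecise in a small trial.

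**3. Shared T1 error.** With unit variances and equal correlations, Cov(T0 − T1, T1 − FU) = ρ − ρ − 1 + ρ = ρ − 1, and each variance is 2(1 − ρ), so the correlation is −0.5. If correlation instead decays with time as AR(1), the covariance is ρ − ρ² − 1 + ρ = −(1 − ρ)² and the correlation is −(1 − ρ)/2: −0.25, −0.10 and −0.05 at ρ = 0.5, 0.8 and 0.9. The sign is stable; the size is not.

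**4. Adding the two interval results.** This recovers the T0-FU point estimate. Its variance also needs the covariance of the two results. Under equal correlations, with each interval's variance V, the correct variance is 2V − 2(0.5V) = V. Treating the intervals as independent gives 2V, a standard error too large by √2 ≈ 1.41.

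**5. Within-group tests.** With equal true effects and power p in each of two arms, the tests disagree with probability 2p(1 − p): 32% at p = 0.2 or 0.8, and at most 50%, at p = 0.5.

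**The case against.** The strongest reply is that T1-FU answers a legitimate question, what happens once treatment stops, and that the Discussion speaks of changes during both the intervention and the follow-up period. The stated research question and the primary outcome are untouched, the study calls itself a pilot, and retained effect at FU is not named as an objective. All of that stands. It supports keeping T1-FU and treating this as a secondary matter. It does not supply the missing contrast.

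A second reply is that the choice of analysis is left open until the data have been checked. That concerns the type of test; the intervals to be compared are already fixed.

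A reader might infer that T1-FU always penalises the better arm. It does not: with full retention it is zero, and with clearly better retention in the larger-gaining arm it favours that arm.

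A reader might also infer that the trial can say nothing about benefit at follow-up. That goes too far. All outcomes are to be measured at T0, T1 and FU, T0 to FU is examined within arms, and the point estimate can be summed. If SDs of the within-arm T0-FU changes were published, a standard error could be rebuilt, but the article promises means, SDs and confidence intervals only where feasible and plans no such comparison.

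Lastly, nothing says that arms will be ranked by whose within-group result is significant. The article plans explicit inter-group comparisons and adds the within-group ones to them, so that misuse is a risk to guard against and not a stated intention.

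**Conclusion.** The concern holds for the secondary follow-up analyses. The outcome definitions and the Group comparison section agree that the arms are compared at follow-up only on change from a post-treatment value, and no between-group estimate with its own standard error is planned for T0 to FU. Under equal partial retention the planned contrast goes against the arm that gained more; under other patterns it may be null or correct. No size can be taken from the article: the 1.5 s and 3.5 s, the percentages, the −0.5 correlation (equal visit correlations only) and the 50% discordance (a maximum) all rest on stated assumptions. The BL-T0 group comparison is uninformative but biases no treatment estimate. The primary T0-T1 result stands as planned. The change is worth making, but the point does not threaten the trial's main conclusion.

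**What to change.** In Table 1, the paragraph defining change over time, the motor task related profile and the Group comparison section:

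- Add the between-group difference at FU adjusted for T0, by ANCOVA or by a repeated-measures model with a T0-FU contrast, for task time and the other outcomes that have a T0 value.
- Use an ordinal or rank-based analogue for the CMSA assistance level and the task stage. Leave out the imagery diary: it is described only for EG1 and EG2 once therapy has begun, so it has no T0 value.
- Keep T1-FU as a description of decay.
- Use BL-T0 to describe retest stability, or BL as a further covariate, without a group test.
- Report within-group changes with confidence intervals and state that they are not used to compare arms.

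The cost is wording. No visit, measurement or patient is added, and one uninformative group test goes.
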